**April 2010**

**Summary**

**Title:**

A randomized, controlled, open label, multicentric clinical trial to evaluate the efficacy and safety of recombinant tumor necrosis factor receptor:Fc fusion protein (rhTNFR:Fc) with methotrexate (MTX) in active rheumatoid arthritis (ReABLE-II)

**Trial Objective:**

Compare the clinical efficacy and the influence on the joint radiology progression between different treatment groups of RhTNFR:Fc combined with MTX and between these groups and the MTX monotherapy.

**Trial Design:**

A randomized, controlled, open-label, multicenter clinical trial.

**Study Subjects:**

Rheumatoid arthritis subjects who meet the inclusion/exclusion criteria randomly divided into 3 groups (Group A, Group B and Group C) using centre-stratified block-permuted randomization with 30 patients in each group and 90 patients in total.

1. Inclusion criteria: Only those subjects who meet all of the following conditions could be included in the trial
2. The subjects diagnosed with rheumatoid arthritis according to the revised 1987 American College of Rheumatology (ACR) Criteria, and with a disease duration of ≥ 6 months.
3. During the screening period and the baseline period, the swollen joint count (SJC) of the subjects should be ≥ 6 (66 joints counted), while the tender joint count (TJC) should be ≥ 8 (68 joints counted); ESR ≥ 28mm/h or CRP ≥ 20 mg/l in laboratory examination; and ≥ 1 bone erosion lesions revealed in X-ray films of both hands/wrists.
4. Subjects aged between 18 and 60 (inclusive) years old;
5. There has been no use of any marketed or non-marketed biological agents for rheumatoid arthritis (focusing on: etanercept, infliximab, adalimumab, rituximab[CD20 McAb], tocilizumab[IL-6 receptor Ab], abatacept[CTLA4-Ig], anakinra[IL-1 antagonist]) before screening;
6. Any DMARDs drugs used other than MTX have been stopped for 4 weeks before the trial; Oral cortical hormones (prednisone ≤ 10 mg/d or its equivalent) and NSAIDs (up to the maximum recommended dose) are allowed, but the dose should be stable for at least 4 weeks before the baseline period;
7. Women of childbearing potential agreeing to take effective methods of contraception during the trial;
8. The urine pregnancy test of women of childbearing age should be negative during screening.
9. Subjects willing to sign the nformed consent form (ICF) and comply with the requirements of the study protocol;
10. Exclusion criteria: Subjects complying with any of the following conditions should be excluded from the trial.
11. Major surgery (including joint surgery) performed within 8 weeks before screening, or major surgery planned within 6 months after enrollment.
12. Patients with rheumatic autoimmune diseases other than rheumatoid arthritis: including systemic lupus erythematosus (SLE), mixed connective tissue disease (MCTD), scleroderma and polymyositis. However, subjects with Sjogren syndrome are allowed to participate in this trial. If ANA is positive, the possibility of SLE should be excluded based on the clinical conditions and the negative result of the anti-DNA antibody test.
13. Rheumatoid arthritis with wrist X-ray being Stage IV.
14. Patients having suffered or suffering from inflammatory arthritis other than rheumatoid arthritis (such as gout, reactive arthritis, psoriatic arthritis, seronegative spondyloarthropathy, Lyme disease).
15. Patients who have received any investigational drug within 4 weeks before screening (or 5 half-life periods, whichever is the longer).
16. Patients who have undergone any cell elimination therapy, including the investigational drug (e.g. CAMPATH, anti-CD4, anti-CD5, anti-CD3 and anti-CDl9).
17. Patients treated with intravenous gamma globulin, plasma exchange or Prosorba plasma separation exchange within 6 months before the baseline,.
18. Patients who have been injected with cortical hormones intraarticularly or by other means within 4 weeks before the baseline.
19. Patients who have received any vaccine within 4 weeks before the baseline.
20. Patients who have used any alkylating agents, such as cyclophosphamide, chlorambucil or total lymphoid irradiation, within 4 weeks before the baseline.
21. Subjects with severe and uncontrolled cardiovascular diseases, neurological diseases, pulmonary diseases (including obstructive pulmonary disease and interstitial lung disease), nephropathy, liver diseases, endocrine diseases (including uncontrolled diabetes) and gastrointestinal diseases, etc.
22. Patients with uncontrolled disease state, such as asthma, psoriasis, inflammatory bowel disease and other diseases, usually requiring oral administration or injection of cortical hormones to treat recurrence.
23. Patients with known currently active or recurrent bacterial, viral, fungal, mycobacterial diseases or other infectious diseases (including but not limited to tuberculosis and atypical mycobacterial diseases, granulomatous diseases shown by chest X-ray, hepatitis B and C, HIV infection, herpes zoster, but excluding onychomycosis infection), or patients requiring hospitalization and intravenous antibiotic therapy within 4 weeks prior to screening or infected patients requiring oral antibiotic therapy within 2 weeks prior to screening.
24. Subjects with a history of malignant tumors, including solid tumors and hematological malignancies (except for patients with cutaneous basal cell carcinoma that has been excised or cured).
25. Pregnant or lactating (breastfeeding) women.
26. Subjects suffering from neuropathy and other painful diseases that may interfere with pain evaluation.
27. Serum creatinine > 1.5 mg/dl.
28. Alanine aminotransferase (ALT) or aspartate aminotransferase (AST) > 2 x ULN (if ALT or AST is measured to be > 2 x ULN for the first time, sampling should be conducted again during the screening period), or total bilirubin > 1 x ULN (if total bilirubin is measured to be > 1 x ULN for the first time, sampling should be conducted again during the screening period).
29. Platelet count < 100 × 109 /L or WBC < 3 × 109 /L.
30. HBsAg or anti-HCV positive

**Test Method:**

The trial is a randomized, controlled, open-label, multicenter clinical study. Qualified subjects after screening will be randomized into 3 groups (Groups A, B and C) using centre-stratified block-permuted randomization, with 30 patients in each group and 90 patients in total:

Group A:

(RhTNFR:Fc + MTX group), 52 weeks; n=30

Group B:

"MTX montherapy"; n=30

(RhTNFR:Fc + MTX group)

Group C:

"MTX monotherapy"; n=30

Baseline

52 weeks

26 weeks

4 weeks

13 weeks

36 weeks

MTX dose increase stage: MTX will be increased from 10 mg/ week to 15 mg/ week

Note: Folic acid at 5mg/ week will be given on Day 2 of MTX administration in the trial.

**Efficacy Observation Indicators:**

Before treatment, 12, 24, 36 and 52 weeks after treatment, the rest pain, morning stiffness duration, swollen joint count and tender joint count , and health assessment (HAQ), subject's assessment of disease, and doctor's assessment of illness will be evaluated.

CRP and ESR will be evaluated before treatment and at 12, 24, 36 and 52 weeks after treatment.

X-ray changes of both wrists (Sharp score) before treatment and 24 and 52 weeks after treatment.

If necessary, MRI before treatment and at Week 52 (15 patients in Group A and 15 patients in Group C respectively; 30 patients in total).

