**5. Test method and course of treatment**

5.1 Test method:

The trial is a randomized, controlled, open-label, multicenter clinical study. Qualified subjects after screening will be randomly divided into 3 groups (Groups A, B and C) using centre-stratified block-permuted randomization, with 30 patients in each group and 90 patients in total:

5.2 Drug usage:

1. In MTX therapy, the initial dose is 10mg/ week, which will gradually be increased to 15 mg/ week (in Week 4);
2. At the same time, 25mg of RhTNFR:Fc (trade name: Yisaipu) will be injected subcutaneously each time, twice a week for treatment.
3. The subjects will be treated with the combined use of MTX according to the above regimen until Week 52, and endpoint evaluation will be conducted. The dose of MTX could be reduced for safety reasons. If the subjects could not tolerate the dose reduction, the event could be recorded as an adverse event. After reduction, the dose could be restored to the prescribed dosage when the investigator thinks it is appropriate.
4. Diagram of drug usage:

Group A:

(RhTNFR:Fc + MTX group), 52 weeks; n=30

Group B:

"MTX monotherapy"; n=30

(RhTNFR:Fc + MTX group)

Group C:

"MTX monotherapy"; n=30

Baseline

52 weeks

24 weeks

4 weeks

12 weeks

36 weeks

MTX dose increase stage: MTX will be increased from 10 mg/ week to 15 mg/ week

Note: Folic acid at 5 mg/ week will be given on the Day 2 of MTX administration in the trial.

5.3 Criteria for drug withdrawal:

If one of the following conditions occurs, the investigator may consider drug discontinuation for observation:

1. A serious adverse event occurs, and it has certain relationship with the investigational drug;
2. An adverse drug reaction occurs, and effective remission cannot be achieved after symptomatic treatment;
3. Laboratory tests: transaminase > 3 times the normal value or WBC < 3×109 /L, or PLT < 100×109 /L;
4. The subject has other diseases, and the investigational drug may aggravate the condition.

5.4 Withdrawal from the trial:

For the patients who withdraw during the trial, the investigator must record the reason and date of withdrawal in detail. Patients who may withdraw during the trial can be divided into the following categories:

- 1. Patients found to fail to meet the inclusion/exclusion criteria during the trial;

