  2. Treatment discontinuation > 4 weeks during the medication due to adverse drug reaction or other reasons (e.g. the treatment has to be discontinued due to occurrence of other disease, migration to other places and loss to follow-up); or within 24 weeks, the accumulated duration of drug discontinuation has exceeded 8 weeks;
  3. Subjects who withdraw the drug by themselves and give up continuing the trial;
  4. Due to serious adverse drug reaction, the drug must be withdrawn in advance.
  5. Those with poor compliance and failing to take the drug according to the schedule or design;
  6. Those with concurrent occurrence of other serious diseases and the investigator considers inappropriate to continue the medication;
  7. Those failing to complete all the examination items as required and thus not evaluable.

5.5 Trial assessments:

The screening visit will be completed within 3 weeks (21 days) before the first administration of the investigational drug. The baseline visit and randomization will be conducted on the day of the first administration, and informal visits will be conducted every 4 weeks to understand the medication and adverse events of the subjects. Formal visits will be conducted every 12 weeks, and the visit results will be recorded. The endpoint visits will be conducted at week 52. In addition to the baseline, the time window for each visit is ±7 days (based on the baseline).

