**100 mm**

6.1.7 Doctor's assessment on the current disease status:

The 100 mm visual analog scale is used to assess the comprehensive disease condition before and after medication. The method of assessment is the same as above.

6.2. Conventional laboratory indicators:

The blood routine examination, biochemical examination, erythrocyte sedimentation rate test (ESR, Wechsler method, normal values: ≤ 15 mm/h for males, ≤ 20 mm/h for females) and C-reactive protein test (CRP, quantitative method) will be conducted before treatment and at week 12, 24, 36 and 52 after treatment.

The urine routine examination will be conducted before treatment and at week 12, 24, 36 and 52 after treatment.

The rheumatoid factor (RF) examination and ANA will be conducted before treatment, and at 24 and 52 weeks after treatment.

The anti-CCP antibody test (2nd generation) will be conducted before treatment.

6.3. Safety observation indicators:

PPD, HbsAg antibody, HCV-Ab and HCV antibody were checked before enrollment. The laboratory indexes to be monitored in the trial included: blood routine, urine routine, liver and kidney function, ANA and chest radiography.

6.4. Imaging observation indicators:

The examinations for both hands include X-ray and MRI of wrist joints, and other parts will be examined if necessary. The Sharp score is used to evaluate the affected joints.

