**7. Efficacy evaluation:**

7.1 Primary endpoints:

Improvement in Sharp score of X-ray of affected joints.

7.2 Secondary endpoints:

1. Proportion of subjects reaching ACR20, ACR50 and ACR70: ACR50 and ACR70 are defined as 50% and 70% improvement respectively using the same criteria as ACR20.
2. Average changes of ACR core parameters relative to the baseline level
3. Average change of HAQ score from baseline to Week 52
4. Time for each treatment group to reach ACR20, 50 and 70
5. The proportion of subjects with low disease activity at each visit
6. The proportion of subjects achieving disease remission at each visit
7. MRI changes (joint space narrowing and bone erosion)

7.2.1 The response definition of ACR20 is: there is 20% improvement in the number of swollen and tender joints (28), as well as 20 % improvement in at least 3 of the 5 following items:

1. The VAS score of pain assessed by the subject;
2. The VAS score of overall disease condition assessed by the subject;
3. The VAS score of overall disease condition assessed by investigator;
4. Health Assessment Questionnaire (HAQ);
5. Acute phase reactant (ESR or CRP).

7.2.2 DAS28:

[figure not shown]
(28 joints)

The disease activity score of 28 joints will be calculated as follows:

DAS28 = 0.56 × + 0.28 × + 0.7 × ln(ESR) + 0.014 × GH

TJC: Tender joint count, SJC: Swollen joint count, ESR: erythrocyte sedimentation rate (in mm/h), GH: general health status expressed in the 100 mm VAS.

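### The protocol gives conflicting accounts of who has MRI, and the only selection criterion for the 15 + 15 subset allows choice after allocation is known

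*Protocol*

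**What the plan says.** Four places in the protocol deal with MRI.

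- **Summary, Efficacy Observation Indicators:** "If necessary, MRI before treatment and at Week 52 (15 patients in Group A and 15 patients in Group C respectively"; the stated total is 30. MRI is conditional, limited to two arms, and capped at a third of the trial.
- **Section 6.4, Imaging observation indicators:** "The examinations for both hands include X-ray and MRI of wrist joints, and other parts will be examined if necessary". Here the conditional phrase belongs to other body parts, not to the wrist MRI. No subset or arm is named.
- **Attachment I, Trial Flow Chart:** MRI is ticked at baseline and Week 52, without a footnote or restriction.
- **Section 7.2, item 7:** "MRI changes (joint space narrowing and bone erosion") is listed as a secondary endpoint, with no population.

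Three design features bear on how a subset could be formed. The Summary describes "A randomized, controlled, open-label, multicenter clinical trial". Section 5.1 allocates patients "using centre-stratified block-permuted randomization, with 30 patients in each group and 90 patients in total". Section 5.5 states: "The baseline visit and randomization will be conducted on the day of the first administration". The flow chart gives the baseline window as Day -7 to Day 0.

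The protocol does not say who chooses the 15 patients per arm, when, or by what rule.

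**The concern.** There are two problems.

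First, the passages disagree on the sample and the arms for a named endpoint. A site working from the flow chart has no reason to leave anyone out. A site working from the Summary would scan some patients in Groups A and C and none in Group B. Seven centres enrol competitively (section 10.1), so different sites could follow different rules. A pre-treatment scan that was not done cannot be recovered later. On the Summary's reading, Group B also contributes nothing to an endpoint that section 7.2 states without an arm limit.

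Second, the Summary's subset has no selection rule beyond necessity. A quota for a pre-treatment scan that is set separately for Groups A and C can be filled exactly only once allocation is known, unless the patients are marked in advance on the randomization list. No such marking is described. Because treatment is open, whatever counts as necessary could be judged differently in the two arms. The scanned patients of Group A and Group C would then not be random samples of their arms, and randomization would no longer protect this comparison.

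**Working it through.** **1. Coverage under each reading**

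- Summary: 15 + 15 = 30, as the protocol says. That is 30/90 = 33% of the trial, 15/30 = 50% of Groups A and C, and 0/30 of Group B.
- Section 6.4 and flow chart, taken without restriction: up to 90/90, all three arms.
- For an A versus C comparison, going from 30 to 15 per arm multiplies the standard error by √(30/15) = 1.41. The plan claims no power for MRI, so this shows only that the two readings differ materially.

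**2. Timing**

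Randomization falls on the first-dose day (section 5.5), and the baseline window runs from Day -7 to Day 0 (Attachment I). A scan done before Day 0 precedes allocation, so the patient's arm is not yet known. With 1:1:1 allocation, obtaining about 15 scanned patients in each of A and C this way means scanning about 45 patients, of whom about 45/3 = 15 would later fall into Group B. Otherwise the choice is made on Day 0, between allocation and first dose. Filling the Summary's quota with no Group B scans therefore points to choice after allocation, although the text does not say so.

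**3. The planning figures borrowed for the illustration**

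Section 9.2 assumes X-ray mTSS changes of -0.5 ± 1.0 (combination) and 2.5 ± 5.0 (MTX), a difference of 3.0, two-sided α of 0.05, and 25 per group for more than 80% power. With root-mean-square SD √((1.0² + 5.0²)/2) = 3.606, n = 2 × (1.960 + 0.842)² × 3.606²/3.0² gives 23 per group. Power at 25 per group is 82.2% (pooled t) or 80.8% (Welch). The stated figure is reproduced and is not in question.

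**4. Illustration of selection bias (X-ray figures, not MRI)**

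Assumptions: in both arms the scanned half is the worse half on a marker that has correlation r with progression, and the variables are normal. The mean of the upper half of a standard normal is √(2/π) = 0.798. The shift in an arm's mean is 0.798 × r × SD, so the net shift in the difference is 0.798 × r × (5.0 − 1.0).

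| r (assumed) | Shift in C | Shift in A | Net shift | Share of 3.0 |
|---|---|---|---|---|
| 0.1 | 0.40 | 0.08 | 0.32 | 11% |
| 0.3 | 1.20 | 0.24 | 0.96 | 32% |
| 0.5 | 2.00 | 0.40 | 1.60 | 53% |

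The same rule in both arms does not cancel out, because the assumed SDs differ. Here the apparent advantage of Group A grows. Selecting the better half would reverse the sign.

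**The case against.** Section 6.4 lists types of examination, and the flow chart is a visit schedule. Neither states a population. The Summary is the only place that gives MRI numbers and arms, so the other two could be read as giving the method and timing for whoever is scanned. A fixed, equal quota also looks more like an optional substudy than patient-by-patient clinical need, and the conditional phrase may govern whether the substudy takes place at all. Scans within the Day -7 to Day 0 window could precede allocation. MRI is the last of seven secondary endpoints.

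Much of this stands, and it rules out several stronger readings:

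- A reader might infer that section 6.4 and the flow chart require MRI in every patient. They only omit a restriction.
- A reader might infer that investigators pick patients on need while knowing the treatment. No section says who chooses, on what basis or when. The documents allow this but do not state it.
- A reader might apply the selection to Group C alone and obtain 0.798 × 0.3 × 5.0 = 1.2 points, or 40% of the planned difference. Nothing in the documents supports selecting in one arm only.
- A reader might treat 15 per arm as an underpowered test. The plan sizes the trial on X-ray mTSS and makes no power claim for MRI.

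The objection does not remove the conflict. No section links the Summary's restriction to 6.4, 7.2 or the flow chart, and no section gives a selection rule. This is a matter of trial conduct that the protocol itself fixes inconsistently, not a detail left to an analysis plan.

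**Conclusion.** The point holds in a limited form. The protocol gives different numbers and arms for a secondary endpoint: 30 patients in Groups A and C, or an unrestricted schedule covering up to 90 in three arms. For the subset, necessity is the only criterion. Together with open-label treatment and arm-specific quotas, this allows selection after allocation is known, so the A versus C MRI comparison may not be a randomized one.

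The size of any bias cannot be derived from the documents. The 0.3 to 1.6 points are an illustration that rests on assumed correlations of 0.1 to 0.5, on exactly the worse half being scanned in both arms, and on X-ray SDs standing in for MRI. They say nothing measured about MRI. The primary X-ray Sharp score endpoint carries no such subset and is unaffected.

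**What to change.** Reconcile the Summary, section 6.4, section 7.2 item 7 and the flow chart on who is scanned, and delete the conditional wording in the Summary. If all patients are meant, correct the Summary.

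If the 15 + 15 subset is kept, choose it by a rule that depends neither on perceived need nor on known allocation, and state the subset in 6.4, 7.2 and the flow chart. There are two workable forms:

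- **A random flag on the randomization list within Groups A and C.** The baseline scan is done between randomization and first dose. No extra scans are needed, but because randomization is on the first-dose day, the scan must be fitted in on that day.
- **A rule fixed at screening, before allocation.** The scan can be done earlier in the baseline window. Some patients later allocated to Group B would also have a baseline scan (about 15, if about 15 are wanted in each of A and C), and the numbers in A and C would be met only approximately.

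Under either form, a few scans may be lost to refusal or contraindication. Otherwise the cost is wording in four places and, for the first form, one extra field on the randomization list.

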**Efficacy Evaluation:**

ACR20\50\70, DAS28, CDAI and SDAI will be compared within and between the groups at week 24 and 52 week after treatment, and Sharp score changes will be compared.

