**2. Trial objective:**

Compare the clinical efficacy and the influence on the joint radiology progression between different treatment groups of RhTNFR:Fc combined with MTX and between these groups and the MTX monotherapy.

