**9. Statistical methods:**

9.1 Selection of statistical analysis data:

Intent-to-treat (ITT): all subjects eligible and enrolled after screening and having taken at least one dose of the drug and received at least one post-treatment effectiveness evaluation; LOCF (last observation carry-forward) will be adopted for those subject’s data not observed during the whole treatment course, that is, estimating the missing values of important indicators using the closest observed data. The ITT analysis will be used in this trial.

Safety population: it includes all subjects having taken at least one dose of the drug and received at least one post-treatment safety evaluation.

9.2 Statistics Analysis Plan:

Statistical analysis will be carried out using the SAS statistical analysis software. A sample size of 90 patients was estimated for the open label period with the assumption that mean mTSS CRF was -0.5±1.0 in the MTX plus rhTNFR:Fc group, and 2.5±5.0 in the MTX group at week 52. A sample size of 25 patients per treatment group was calculated to be necessary for more than 80% power to reject the null hypothesis of no difference among the treatment groups with an α of 0•05. Assuming loss of patients, the study required a minimum of 30 patients in each group. Two-sided test will be used for all statistical tests, and the difference tested will be considered as statistically significant if the P value is equal to or less than 0.05. Measurement data will be statistically described using mean±SD (standard deviation). Paired t-test will be used for intra-group differences before and after the treatment. Enumeration data will be statistically described using frequency (constituent ratio).

Dropout analysis: Calculate the dropout rates and the rates of dropout due to AE.

Efficacy analysis: The paired t test or nonparametric test or chi-square test will be used to evaluate the efficacy indexes.

Safety analysis: Calculate the incidence rate of adverse events and tabulate the AEs occurring during the trial, normal/abnormal changes in laboratory findings before and after the trial, as well as relationships of abnormal changes with the investigational drug

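### No clinical measure is singled out to carry the clinical-efficacy half of the objective, while 12 clinical tests per pair of arms are each judged at P≤0.05

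*Protocol*

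**What the plan says.** The objective (protocol section 2, repeated in the Summary) has two parts: "Compare the clinical efficacy and the influence on the joint radiology progression between different treatment groups". Section 7.1 gives one primary endpoint, which is radiographic: "Improvement in Sharp score of X-ray of affected joints". The sample size in 9.2 also rests on the radiographic score alone.

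The clinical measures appear in two places:

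- **Summary, Efficacy Evaluation.** ACR20, ACR50 and ACR70 head a list that continues "DAS28, CDAI and SDAI will be compared within and between the groups at week 24 and 52 week after treatment".
- **Section 7.2, secondary endpoints.** The first entry is "Proportion of subjects reaching ACR20, ACR50 and ACR70", with no week given. The list also has changes in the ACR core parameters, HAQ change to Week 52, time to ACR response, "The proportion of subjects with low disease activity at each visit", "The proportion of subjects achieving disease remission at each visit", and MRI changes.

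The two lists do not match. CDAI and SDAI are compared in the Summary but do not occur in section 7. DAS28 is defined in 7.2.2 but is not among the seven listed secondaries.

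Section 9.2 makes all tests two-sided and gives one criterion: "the difference tested will be considered as statistically significant if the P value is equal to or less than 0.05". The protocol names no key secondary, no order among the secondaries and no adjustment.

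**The concern.** Because the primary endpoint is radiographic, whatever the trial concludes about clinical efficacy must come from the secondaries. Six overlapping clinical measures are compared at two weeks, and all are judged by the same P≤0.05 criterion. These results can disagree: ACR20 might reach P≤0.05 at Week 24 only, or SDAI might do so when CDAI does not. The protocol does not say which result then decides. The one to highlight could be chosen once the data are in, and the 0.05 attached to it would not be the error rate of the clinical conclusion.

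This is multiplicity over measures and weeks. It remains after a single pair of arms has been fixed, and it is separate from the question of which of the three arms are compared.

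**Working it through.** **The plan's own figure.** The protocol gives no error rate for the clinical measures. Its only statistical figure is the sample size for the radiographic score in 9.2: means -0.5 (SD 1.0) and 2.5 (SD 5.0), two-sided 0.05, and 25 per group for more than 80% power.

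- Difference = 2.5 - (-0.5) = 3.0. Pooled SD = √((1.0² + 5.0²)/2) = 3.606.
- Normal approximation: power = Φ(3.0 / (3.606 × √(2/25)) - 1.96) = Φ(2.942 - 1.96) = 83.7%.
- Welch t test: 79.1% at 24 per group, 80.8% at 25.

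The figure reproduces, but it concerns the primary endpoint only.

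**Number of clinical tests.** For one pair of arms, counting only the between-group comparisons that the Summary schedules: 6 measures (ACR20, ACR50, ACR70, DAS28, CDAI, SDAI) × 2 weeks (24, 52) = 12. Within-group tests are not counted.

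**Independent tests, no true effect.** P(at least one P≤0.05) = 1 - 0.95¹² = 1 - 0.540 = 46.0%.

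**Correlated tests.** The protocol gives no correlations, so they are assumed. For 12 two-sided z tests with common correlation r and c = 1.96:

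P = 1 - ∫ φ(u) · [Φ((c - √r·u)/√(1-r)) - Φ((-c - √r·u)/√(1-r))]¹² du

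| Assumed r | P(at least one) | Multiple of 5% |
| --- | --- | --- |
| 0 | 46.0% | 9.2 |
| 0.3 | 39.7% | 7.9 |
| 0.5 | 31.9% | 6.4 |
| 0.7 | 23.2% | 4.6 |
| 0.9 | 13.5% | 2.7 |

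A simulation of 200,000 replicates agrees: 39.5%, 31.9%, 23.1% and 13.6% for r = 0.3, 0.5, 0.7 and 0.9.

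**Separate correlations for measures and weeks.** With a between-week correlation of 0.3 to 0.7, the chance is 33–37% at a between-measure correlation of 0.5, 26–30% at 0.7, 22–25% at 0.8 and 17–20% at 0.9.

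**Patient-level check.** This simulation used 30 per arm, chi-square tests for the ACR responses and t tests for the indices. Assumptions: ACR20/50/70 rates of 60%, 35% and 15%; correlations of 0.9 to 0.97 among DAS28, CDAI and SDAI; 0.5 to 0.8 between these and ACR response; 0.4 to 0.8 between visits. The 12 tests give 26–33%.

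**One direction only.** Counting only false results that favour one given arm, the 12 tests give 16.0% at r = 0.5, 11.6% at 0.7 and 9.2% at 0.8. The single-test level is then 2.5%.

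**The case against.** **The protocol does have a hierarchy.** This stands. Section 7.1 names one primary endpoint, section 7.2 labels its measures secondary, and the sample size rests on the radiographic score. What is missing is any order among the clinical measures. A reader who inferred that the trial's main conclusion is at risk would be wrong.

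**Week 52 is a fixed endpoint.** This also stands. Sections 5.2 and 5.5 put the endpoint evaluation at Week 52, and 7.2 ties the HAQ change to it. So it would be wrong to say that the protocol has no endpoint time. However, the Summary puts Week 24 beside Week 52 for all six clinical measures without saying which decides.

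**No passage says that one significant secondary proves clinical efficacy.** Correct. Section 9.2 defines when a difference is called significant; that any one result would suffice for a clinical claim is an inference. The 14–40% is therefore the chance of at least one nominally significant result, not of a formally declared false claim. The protocol leaves room for the inference because it names no deciding result.

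**Is a false clinical finding likely?** A reader might infer this, but the figures do not support it. Even 12 independent tests stay below one half, and the definitions point to strong overlap: ACR50 and ACR70 use the ACR20 criteria, and DAS28 shares components with them.

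**Should the per-visit proportions be counted?** Low disease activity and remission at four visits ("CRP and ESR will be evaluated before treatment and at 12, 24, 36 and 52 weeks after treatment" gives the weeks) would add 8 tests, making 20. But 7.2 only lists these as proportions, and the Summary schedules between-group comparisons at Weeks 24 and 52. The larger count is not used here.

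**A separate analysis plan could set the order.** It could, and a protocol silent on the matter would be no finding. This protocol is not silent: 9.2, itself headed as the statistical analysis plan, applies one significance criterion to every difference tested. A later ordering would have to qualify that sentence.

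**Open-label conduct makes it worse.** That adds little here. Results can be selected after the fact in a blinded trial too, and section 5.7 keeps joint assessors from the subjects' other data.

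**Conclusion.** The point holds as a weakness in the secondary clinical evidence. Clinical efficacy is half of the objective, no clinical measure is named to decide it, and each of 12 scheduled between-group tests per pair of arms is judged at two-sided P≤0.05. With no true effect, the chance of at least one nominally significant clinical result is about 14% to 40% for a common correlation of 0.9 to 0.3, and 46% if the tests are independent. At the most favourable correlation shown, this is still 2.7 times 5%.

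The size depends on the assumed correlations and on a single fixed pair of arms; the protocol supplies neither. That the rate exceeds 5% does not depend on the exact correlation within the range shown. The primary Sharp conclusion and its sample size are not affected.

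**What to change.** In 7.2 and 9.2:

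1. Name one clinical measure at Week 52, the endpoint visit, for one named pair of arms, as the key secondary on which the clinical-efficacy claim rests. ACR20 is an example; the choice is the sponsor's.
2. Test it at two-sided 0.05 only if the primary is significant. For this gate to work, the primary test must also name its pair of arms.
3. State that all other clinical measures, the Week 24 comparisons and the per-visit proportions are supportive: estimates with 95% confidence intervals and nominal P values, without a claim of significance.
4. If no key secondary is chosen, apply item 3 to all secondaries.

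The named clinical test then has a false-positive rate of at most 5% for its pair of arms. Keeping all 12 tests confirmatory would instead need, by Bonferroni, 0.05/12 = 0.0042 per test.

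The change needs no extra patients, visits or data. Its cost is that isolated nominal results on other indices or visits can no longer be presented as significant and, if the gate is used, that the clinical claim depends on the primary succeeding.
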